## Abstract

**Background:**

Chronic kidney disease (CKD) is characterized by long-term structural or functional kidney abnormalities, often progressing over decades and potentially leading to kidney failure, treatable only by dialysis or transplantation. Nutritional programs (NPs), physical activity (PA) programs, and mindfulness programs (MPs) can play a key role in conservative CKD management, aiming to slow the progression of symptoms, decrease drug load, reduce stress, and delay dialysis. KidneYou (Advice Pharma Group Srl) integrates nutrition, exercise, and MPs to improve the health of patients with CKD by promoting lifestyle changes and stress reduction. As an innovative medical tool, KidneYou is designed to address an unmet need by providing a nonpharmacological approach for better managing CKD, empowering patients to manage their condition more effectively and sustain a healthier lifestyle, which could ultimately lead to improved disease outcomes.

**Objective:**

This study aims to evaluate the efficacy and safety of KidneYou, a digital medical device that delivers personalized NPs, PA programs, and MPs to patients with CKD, in comparison with the standard of care.

**Methods:**

This is a multicenter, open-label, randomized, parallel-arm trial aimed at evaluating health improvement in patients with CKD exposed to a nonpharmacological treatment involving an NP, PA program, and MP delivered to the patient by digital technology (investigational arm) or a standard approach (paper diary and control arm) for 3 months. The primary aim of the study is to evaluate the efficacy of KidneYou, defined by the achievement of at least 1 of the 3 conditions described in the composite primary end point: a reduction of at least 10% of azoturia (gram per 24 h), an increase of at least 15% of distance (meters in the 6-min walk test), or a decrease of at least 10% of perceived stress in CKD KidneYou app users compared to CKD KidneYou app nonusers after 3 months.

**Results:**

Data will be analyzed and presented in accordance with international CONSORT (Consolidated Standards of Reporting Trials) guidelines. Recruitment began in July 2022 and stopped at all sites in April 2024. Data analysis is currently ongoing. The results are expected to be published in early 2026.

**Conclusions:**

The results of this trial will guide further studies on the impact of digital devices to help patients with CKD in improving their condition more effectively and sustain a healthier lifestyle, which could ultimately lead to improved disease outcomes.

## Introduction

Chronic kidney disease (CKD) is a progressive condition defined by structural or functional abnormalities of the kidneys with health implications, persisting for over 3 months [1]. It is classified based on cause, glomerular filtration rate (GFR) category, and albuminuria category and includes various disorders that affect kidney structure and function, with diverse clinical presentations depending on the cause, severity, and progression rate. While some forms of CKD progress rapidly, most evolve over decades. Kidney failure, the most serious outcome, can only be treated with dialysis or transplantation [1]. Moreover, CKD is linked to an increased risk of acute kidney injury, which can worsen outcomes and accelerate CKD progression. Early identification and referral for specialized care can improve both clinical and economic outcomes [1].

Adherence to lifestyle interventions in patients with CKD presents persistent challenges, as patients often contend with physical, emotional, and cognitive barriers that impede consistent engagement with recommended dietary, exercise, and stress management routines. Digital health tools, particularly mobile apps, represent a promising solution to improve adherence by offering tailored, accessible support. With smartphone use increasingly widespread, these platforms can provide patients with CKD with real-time, personalized guidance, enhancing both engagement and self-management.

The nutritional program (NP) is an important component of the conservative management of patients with CKD, which precedes and integrates the pharmacological therapies. Generally, the objectives of NP are to maintain an optimal nutritional state, prevent or correct the signs, symptoms, and complications related to chronic renal insufficiency, and delay the start of dialysis. In addition, NP enables a reduction in the drug load (and related side effects and interactions) and can allow for safe and effective use of lower doses of dialysis, even when the GFR continues to diminish [2]. The aim of NP is to provide patients with CKD with an adequate caloric intake, control the sodium and potassium intake, and reduce phosphate intake. Beyond the quantitative aspects, dietary support also calls for modification in the quality of food, favoring foods of plant origin, which induce favorable effects on phosphate metabolism and acid-base balance, with better control of arterial pressure and renal hemodynamics [2,3]. Physical exercise in patients with CKD is another nonpharmacological tool aimed at improving health in this patient population. Despite large scientific evidence produced over the years about exercise tolerance and training among patients on dialysis, individuals with nondialysis-dependent CKD have been relatively understudied, perhaps because of the heterogeneity of the CKD population [4,5]. The clinical evidence produced for individuals with CKD is limited in both quality and quantity. Data from uncontrolled studies and small randomized controlled trials showed that exercise training results in improved physical performance and functioning. Of note, although the current literature does not allow for drawing definitive conclusions about the role of exercise training on the progression of CKD, no study has reported worsening of kidney function as a result of exercise training. Exercise appears to be safe in patients with CKD if begun at moderate intensity and increased gradually. The evidence suggests that the risk of remaining inactive is greater [6].

The mindfulness program (MP) aims to reduce stress perceived by patients with CKD and to improve their coping capacities in response to the psychological burden caused by living with an active chronic disease, the complexity of ongoing therapies, including concomitant ones, and the lifestyle changes required by dietary and exercise programs. Scientific evidence has shown that, when a stress-coping program based on mindfulness meditation is applied to stressed individuals, a significant reduction in perceived stress, anxiety, and depression is observed [7-9].

While the benefits of nutritional counseling, physical activity (PA) promotion, and behavioral support have been extensively demonstrated as stand-alone interventions, growing evidence suggests that integrating them in multicomponent lifestyle programs, particularly when supported by digital tools, may enhance patient engagement and lead to more sustained health improvements over time [10]. Despite the growing availability of digital tools, few interventions specifically designed for patients with CKD combine nutritional guidance, PA promotion, and stress management into a single, integrated platform [11].

The KidneYou app (Advice Pharma Group Srl) is an investigational medical device intended to administer these 3 nonpharmacological programs simultaneously to patients with CKD, to monitor patients’ performance and adherence during the study, and to improve their health status.

The aim of this study is to determine whether the investigational medical device KidneYou, randomly assigned to patients with CKD (G3b or G4 categories; A1 or A2 or A3 categories), can improve the CKD-related health conditions by positive changes in the patient’s lifestyle (ie, healthy eating and PA participation) and by means of cumulative stress reduction (ie, MP) originating from the underlying chronic disease and from diagnosis and treatment interventions necessary to manage it.

## Methods

### Study Intervention

KidneYou, an app for mobile devices developed by Advice Pharma Group Srl, on its electronic data capture (EDC) ICE technology, is an investigational medical device designed to deliver digital therapy (DT) to patients. DT, as part of digital health, uses high-quality digital technologies to stimulate lifestyle changes in patients.

A multidisciplinary board, composed of clinicians, nutritionists, psychiatrists, and graphic designers, has been established. The team worked collaboratively to map out the patient journey for individuals with CKD, identifying key stages within the disease management process. From this journey, critical touchpoints and challenges in CKD management were pointed out, emphasizing factors that play a pivotal role in improving patients’ physical and mental well-being.

Each specialist contributed to defining the core domains of the app. Nutritionists were involved in personalized NPs based on patients’ characteristics and needs, whereas psychiatrists contributed to the design of mindfulness practices tailored to address mental health challenges in patients with CKD. Physiatrists played a crucial role in developing the PA components, ensuring that exercise regimens were safe, effective, and adaptable to individuals with CKD.

Using these multidisciplinary inputs, a computational framework that generates a personalized algorithm was developed, incorporating customized nutrition, PA, and mindfulness strategies, all tailored to individual needs based on their specific health parameters.

To further enhance patient engagement, gamification elements were incorporated into the app design. These features were carefully crafted to encourage consistent app usage and promote a more interactive and enjoyable experience. By turning health management into an engaging activity, the app aims to foster long-term adherence to the prescribed treatment plan.

The overall design of the app reflects a patient-centered approach, combining clinical expertise from multiple fields with innovative digital solutions. This ensures that patients with CKD receive a comprehensive, holistic management experience that is both scientifically grounded and tailored to their specific needs.

KidneYou has been designed to improve the commitment of patients in following clinical directives by working on three therapeutic areas: NPs, PAs, and MPs. All these programs are administered by means of DT for patients included in the intervention group. Images of KidneYou are presented in Figure 1.

The NP assigned by the app is based on gender, BMI, and estimated GFR (eGFR; values both measured at baseline) and is a customized low-protein dietary plan. The plan includes 5 daily meals, which vary every day of the week to maintain the proposed meals attractive for the patient and increase their compliance with the dietary plan. In addition, the NP proposes to each patient further daily alternatives to the first and second courses and side dishes to further augment food variability, reduce as much as possible dietetic monotony, and minimize abandonment or severe deviation from the assigned diet.

The PA assigned by the DT is based on an individual’s background fitness level and patient with CKD history, assessed at baseline. The exercise program is customized in terms of recommended type of PA, minutes of exercise per day, number of days per week, and level of intensity. At the end of each daily exercise, the patient selects the real number of minutes they spent exercising and rates the PA as too light, very good, or too heavy.

The MP aims to help patients follow stress-reducing activities; it consists of multimedia content (audio files) with different mindfulness meditation paths, allowing the patient to be guided by the therapist’s voice through different forms of exercise (eg, breath control, body scan, and virtual sound environments), all aimed at containing stress.

**Figure 1. F1:**
[figure not shown]
Login page of KidneYou (Advice Pharma Group Srl).

### Study Design

This is a multicenter, randomized, 2-arm, comparative, parallel, open-label, premarket study on individuals affected by CKD belonging to GFR categories G3b or G4, and with persistent albuminuria categories A1, A2, or A3 (A3 limited to >300 mg/g [>30 mg/mmol] and <3000 mg/g [<300 mg/mmol]).

This study is a premarket clinical investigation conducted in accordance with European Union Medical Device Regulation n.2017/745 requirements, with the goal of generating clinical evidence necessary for Conformité Européenne marking of the investigational medical device.

Enrolled participants are randomly allocated in a ratio of 1:1 to one of the two treatment arms using a randomization list that is computer generated by the trial statistician and provided through a web-based approach (via interactive response technology or randomization and trial supply management): group A (KidneYou users; investigational arm) or group B (KidneYou nonusers; control arm). A randomization list with random permuted blocks of different sizes (2 or 4 or 6 or 8) has been prepared and included in the electronic case report form (eCRF).

### Ethical Considerations

The study is conducted under the clinical investigation plan and international guidelines, including the most recent versions of the Declaration of Helsinki, the International Conference on Harmonization guidelines for Good Clinical Practice, European Union Medical Device Regulation 2017/745, and International Organization for Standardization (ISO) 14155, as well as all applicable local laws and regulations. The study was approved by the Territorial Ethics Committee (Comitato Etico Territoriale Regione Puglia of the Azienda Ospedaliero-Universitaria Consorziale Policlinico Di Bari, Institutional Ethics Committee protocol number 0036279, April 19, 2022) and by the Italian Ministry of Health (protocol number 2061; October 19, 2022). Informed consent is collected from all the participants involved in the study. No financial compensation was provided to the participants. All participant data are collected in a pseudonymized form and treated confidentially in compliance with applicable privacy laws, including the General Data Protection Regulation. Data are stored securely and used solely for research purposes.

The study team disseminates the trial results by making a summary publicly available on ClinicalTrials.gov, presenting findings at national and international conferences, and publishing them in peer-reviewed journals.

### Treatment Arms

In the intervention group (group A), the NP and PA program are administered through KidneYou, supplemented by guided stress-reduction activities.

In the control group (group B), the NP and PA program are administered by means of a paper diary. No indications are given to patients in this group regarding stress reduction activities.

### Duration of Study

For each patient, the treatment lasts for 3 consecutive months (12 wk), during which lifestyle changes are implemented with or without KidneYou. At the end of this period, the lifestyle program ends, followed by a follow-up visit 1 month later (at 16 wk).

### Study Setting

The trial involves 12 Italian clinical centers, all specialized in the treatment of renal diseases, distributed across different Italian regions, and provides a comprehensive representation of the country’s diverse lifestyles and dietary habits. A detailed list of the participating sites and their respective staff can be found in Multimedia Appendix 1.

### Study Population

The inclusion and exclusion criteria are presented in Textbox 1.

Textbox 1.Inclusion and exclusion criteria.
**Inclusion criteria**
Age ≥18 years at the time of signing informed consent.Participants with chronic kidney disease classified as glomerular filtration rate (GFR) category G3b (30-44 mL/min/1.73 m²) or G4 (15-29 mL/min/1.73 m²); persistent albuminuria category A1 (<30 mg/g), A2 (30-300 mg/g), or A3 (>300 mg/g and <3000 mg/g).Presence of at least 1 causal etiology: diabetes, arterial hypertension, chronic glomerulonephritis, and cystic kidney diseases (eg, polycystic kidney, nephronophthisis, cortical or tubular glomerular cysts, renal medulla cystic diseases, and tuberous sclerosis).Abnormalities of kidney function (GFR and albuminuria) and structure (causal etiologies) present for >3 months with health implications.Perceived Stress Scale total score >12.Sex: male and female.Capability of giving informed consent, including compliance with requirements and restrictions.Ownership of a mobile phone, willingness to use mobile apps, and ability to download KidneYou.Native speakers of Italian or foreign individuals with a full understanding of Italian (all programs provided in Italian).
**Exclusion criteria**
Medical conditions: (1) acute and chronic joint disease; (2) acute or chronic muscle diseases; (3) history or current depression; (4) sleep disturbance; (5) suicidal ideation or any mental disorder; (6) refusal or inability to follow dietary rules; (7) chewing disorder; (8) lack of motivation to follow nutritional program, physical activity, and psychological programs; (9) positive hepatitis C antibody, hepatitis B virus surface antigen or core antibody, Child-Pugh class C, and HIV positive; (10) drug or alcohol abuse; (11) QT-interval prolongation or congenital long QT-interval syndrome and history of arrhythmia; (12) cancer; and (13) autoimmune diseases, Addison disease, and amyloidosis.Prior or concomitant therapies and other exclusions: (1) any change, termination, addition, or replacement of medication in the current treatment strategy; (2) participation in another clinical study in the last 6 months; (3) involvement in the planning or conduct of the study; (4) investigator judgment that participation is not advisable; (5) previous enrollment or randomization in this study; (6) currently pregnant or breastfeeding (women only); and (7) any other condition making participation undesirable in the investigator’s opinion.

### Main Objectives and End Points

#### Primary Objective

The primary objective is (1) to improve the quality and quantity of dietary intake in patients using KidneYou compared to patients not provided with the app after 3 months of a customized NP, (2) to increase energy expenditure in patients using KidneYou compared to patients not provided with KidneYou after 3 months of a customized PA program, or (3) to relieve the stress related to the underlying CKD condition in patients using KidneYou compared to patients not using KidneYou after 3 months of study.

#### Secondary Objectives

The secondary objectives are as follows:

To help patients achieve 2 or more of the aforementioned objectivesTo describe each primary objective achieved in each randomized groupTo stratify the primary objective results by G3b and G4 categories of CKD classificationTo stratify the primary objective results by A1, A2, and A3 (A3 limited to >300 mg/g [>30 mg/mmol] and <3000 mg/g [<300 mg/mmol]) category of CKD classificationTo assess the degree of azoturia reduction (gram per 24 h) in each treatment group during the studyTo assess differences in azoturia reduction (gram per 24 h) between the 2 randomized groups during the studyTo assess the degree of physical function improvements in each treatment group during the 6-minute walk test (6-MWT)To assess differences in physical function improvements between the 2 randomized groups during the studyTo assess the degree of PA increase (min) in each treatment group during the studyTo assess the degree of stress reduction (Perceived Stress Scale [PSS] of Cohen [12]) in each treatment group during the studyTo assess the differences in stress reduction (PSS of Cohen) between the 2 randomized groups during the studyTo detect the acceptability level among KidneYou users.

#### Safety Objective

The safety objective is to describe the safety profile in the 2 treatment groups.

#### Primary End Point

The primary end point is as follows: (1) to evaluate the achievement of a mean reduction of at least 10% of azoturia (gram per 24 h) in CKD KidneYou users exposed to a 3-month NP compared to CKD KidneYou nonusers exposed to the same 3-month NP, (2) to evaluate the achievement of a mean increase of at least 15% of the distance (meters in the 6-MWT) in CKD KidneYou users exposed to a 3-month PA program compared to CKD KidneYou nonusers exposed to the same 3-month PA program, or (3) to evaluate the achievement of a mean decrease of at least 10% of perceived stress (according to the PSS of Cohen) in CKD KidneYou users exposed to a 3-month MP compared to CKD KidneYou nonusers and not exposed to the same MP.

#### Secondary End Points

The secondary end points are as follows:

To evaluate the achievement of 2 or more of the aforementioned components of the primary end pointTo assess the achievement of every single component of the primary end point in each randomized groupTo stratify the within-group changes and the between-group differences in changes of primary end point results by the eGFR category of patients with CKD (eg, G3b and G4)To stratify the within-group changes and the between-group differences in changes of primary end point results by the albuminuria category of patients with CKD (eg, A1, A2, and A3)To assess the within-group changes of mean values of azoturia (gram per 24 h) in each treatment group during the study visits (ie, V0, V2, and V3)To assess the between-group differences in changes of mean values of azoturia (gram per 24 h) during the study visits (ie, V0, V2, and V3)To assess the within-group changes of mean values of heart rate (HR), blood pressure (mm Hg), and O_2_ saturation in each treatment group during the performance of the 6-MWTsTo assess the between-group differences in changes in mean values of HR, blood pressure (mm Hg), and O_2_ saturation during the performance of the 6-MWTsTo assess the within-group changes in mean values of PA (min) self-reported by patients in each treatment group during the study visits (ie, V0, V2, and V3)To assess the within-group changes of mean values of stress reduction (according to the PSS of Cohen) in each treatment group during the study visits (ie, V0, V2, and V3)To assess the between-group differences in changes of mean values of stress reduction (according to the PSS of Cohen) during the study visits (ie, V0, V2, and V3)To assess patient satisfaction with the KidneYou App by using the Net Promoter Score system. With a score ≥7, the participant will be considered a promoter of the app

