#### Primary Analysis on Primary End Point

The primary efficacy end point is the percentage of achievement of a mean reduction of at least 10% of azoturia (grams per 24 h) or the achievement of a mean increase of at least 15% of distance (meters in the 6-MWT) or the achievement of a mean decrease of at least 10% of perceived stress (according to the PSS of Cohen) in KidneYou users exposed to a 3-month NP, PA program, and MP compared to KidneYou nonusers and not exposed to the same 3-month programs.

The observed percentages (in KidneYou users vs KidneYou nonusers) will be tested using a chi-square test or the Fisher exact test, as appropriate.

The secondary analyses on the primary end point include (1) achievement of each single component of the primary end point in each randomized group, (2) achievement of 2 or more of the aforementioned components of the primary end point, and (3) assessment of between-group differences in primary end point results by estimated eGFR category of patients with CKD (eg, G3b and G4) and by albuminuria category of patients with CKD (eg, A1, A2, and A3).

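### The secondary objectives on 6-MWT physical function have no overall continuous end point for distance walked; the continuous 6-MWT end points are heart rate, blood pressure and O2 saturation

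*Protocol article*

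**What the plan says.** All references are to the protocol article.

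- **Main Objectives and End Points, Secondary Objectives.** Two objectives concern physical function: the degree of improvement in each group in the 6-MWT, and the difference in improvement between the randomized groups. Increase in physical activity in minutes is a separate objective.
- **Main Objectives and End Points, Secondary End Points.** The within-group 6-MWT item covers "within-group changes of mean values of heart rate (HR), blood pressure (mm Hg") and O2 saturation. A parallel item covers between-group differences in the same three variables. Distance is not named in either.
- **Same list, the other two primary components.** Azoturia has a within-group item and a between-group one: "To assess the between-group differences in changes of mean values of azoturia (gram per 24 h) during the study visits". Perceived stress (PSS) has the same pair, the second being "To assess the between-group differences in changes of mean values of stress reduction (according to the PSS of Cohen) during the study visits". Both are tied to V0, V2 and V3.
- **Primary End Point.** Distance appears as "a mean increase of at least 15% of the distance (meters in the 6-MWT").
- **Statistics, Primary Analysis on Primary End Point.** "The observed percentages (in KidneYou users vs KidneYou nonusers) will be tested using a chi-square test or the Fisher exact test, as appropriate". A secondary analysis covers "achievement of each single component of the primary end point in each randomized group".
- **Tertiary or Exploratory End Points.** Distance is not listed.

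**The concern.** An objective about improvement needs an end point on which improvement can be recognised. Heart rate, blood pressure and saturation during a self-paced walk do not provide this. A patient who walks farther may finish with a higher heart rate, and the article states no favourable direction for any of the three. Followed as written, the plan would answer a question about physical function with three variables of uncertain meaning and a yes/no rate at a 15% threshold.

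The gap also makes the report uneven. Readers will want to know which component drives a difference in the composite. For azoturia and stress they would get a mean change and a between-group difference. For walking they would get only the proportion above the threshold, with no estimate in metres.

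**Working it through.** **1. Overall continuous end points for each primary component** (secondary and exploratory lists)

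| Component | Within group | Between groups | Responder analysis |
|---|---|---|---|
| Azoturia (g/24 h) | yes | yes | at least 10% reduction |
| PSS | yes | yes | at least 10% decrease |
| 6-MWT distance (m) | none | none | at least 15% increase |

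The count is 2, 2 and 0. Self-reported activity minutes do not fill the gap, because they serve an objective of their own.

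**2. The article's own figure, which supplies the n used below.** The Sample Size Calculation gives 95 per group for 40% v 60%, alpha 0.05 and power 80%. The unpooled formula reproduces it:

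n = (1.960 + 0.842)² × (0.4×0.6 + 0.6×0.4) / 0.20² = 7.849 × 0.48 / 0.04 = 94.2, rounded up to 95.

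The pooled formula gives 97. Nothing in this point changes the figure.

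**3. What a continuous distance end point could add.** The article gives neither an SD nor an expected mean change for distance. The inputs here are assumptions: normally distributed percentage change, equal SD in both arms, 95 per arm, two-sided alpha 0.05.

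- Continuous comparison: power = Φ(δ / (SD·√(2/95)) − 1.96)
- Responder rate in an arm with mean m: p = 1 − Φ((15 − m)/SD)
- Responder comparison: power = Φ((|p1 − p0| − 1.96·se0)/se1), where se0 uses the pooled rate and se1 the two separate rates

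Assumed mean changes of +2% (control) and +10% (KidneYou):

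| SD (points) | Responders, control v KidneYou | Power, continuous | Power, responder |
|---|---|---|---|
| 10 | 9.7% v 30.9% | about 100% | 96% |
| 15 | 19.3% v 36.9% | 96% | 78% |
| 20 | 25.8% v 40.1% | 79% | 56% |
| 25 | 30.2% v 42.1% | 60% | 40% |

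A second case assumes 0% v 5% with SD 12:

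- Continuous: 5/12 = 0.417; 0.417 × √(95/2) = 2.87; power = Φ(2.87 − 1.96) = 82%.
- Responder: p0 = 1 − Φ(1.25) = 10.6%; p1 = 1 − Φ(0.833) = 20.2%; unpooled se = √((0.1056×0.8944 + 0.2023×0.7977)/95) = 0.0519; 0.0967/0.0519 = 1.86; power = Φ(1.86 − 1.96) = 46% (45% with the pooled null variance).

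**4. Share of information lost.** This is one minus the squared ratio of the expected test statistics, with the unpooled se. In the second case it is 1 − (1.86/2.87)² = 58%. In the table's cases it is about 53%, 44%, 40% and 39% for SD 10, 15, 20 and 25.

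**The case against.** Four points can be made on the other side.

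**Some analysis of distance exists.** A reader might infer that the trial has no continuous walking-distance comparison at all. The article does not support that. The Secondary End Points list includes within-group changes, and between-group differences in changes, of the primary end point results by eGFR and by albuminuria category. The Primary End Point section words the distance component as a mean increase in metres, so these items may cover continuous change in distance within strata. The Primary Analysis section, however, treats the stratified item as a secondary analysis of a percentage-based end point, so the reading is ambiguous. At best it gives stratum results and no overall one.

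**The mapping is inferred.** Nowhere does the article say that heart rate, blood pressure and saturation are the only end points for the physical-function objectives. The single-component responder rate also bears on them. It would therefore be too strong to say that the objectives cannot be answered. They have a dichotomised answer on distance and no overall continuous one.

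**The loss may be small.** A reader might also infer that dichotomising discards most of the information. That depends on the assumed SD and effect: the share runs from 39% to 58% in the cases shown. At SD 10 with +2% v +10%, both analyses have ample power.

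**An article condenses.** The clinical investigation plan and any SAP are not shown, and the Secondary End Points section under Statistics already allows percentage change and mixed models. This helps only in part. The article lists its end points one by one and names other variables for the 6-MWT, and the methods apply to listed end points.

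**Conclusion.** The point holds in a limited form. No overall continuous end point for 6-MWT distance is named, although two secondary objectives call for one and the other two primary components each have theirs. The 6-MWT variables that are named have no stated direction of improvement.

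This is a moderate point about secondary objectives. It does not touch the primary test, the 95 per group or the 210 enrolled. Distance at baseline and 3 months must be recorded, since the primary component needs both, so the gap is in what is named for analysis and not in what is measured.

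The objective-to-end-point mismatch rests on the text alone. The power comparison rests on assumed means and SDs and shows the direction of the loss, not its size in this trial.

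**What to change.** Name the within-group change and the between-group difference in change of 6-MWT distance (metres) from V0 to V2 as the end point for the two physical-function objectives. Analyse it by the methods already given in the Secondary End Points section under Statistics. Add V3 only if the test was done then: the Assessments section says all patients undergo the 6-MWT but does not give the visits. Keep heart rate, blood pressure and O2 saturation as measures of physiological response to the test. State whether the stratified items on changes in primary end point results mean continuous changes or responder percentages.

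The cost is one added end point from data already needed, with no new procedure. Timing is the real constraint. The trial is open-label, recruitment ended in April 2024 and analysis is reported as ongoing. The addition should therefore be dated and, if made after outcome data by arm were seen, labelled post hoc. If the clinical investigation plan or SAP already names the end point, citing that dated text settles the matter.
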